### Work package 3: Health impacts

We will assess the extent to which implementation of the B-CAP impacts on health outcomes, using a quasi-experimental interrupted time series design with our Connected Bradford (cBradford) and BiB data sets. We will compare trends of health outcomes collected for 3 years pre, and 3 years post implementation (minimum 6 years data). Using the cBradford dataset, in WP3A we will explore changes in a range of health outcomes across the life-course up to 3 years post implementation using a segmented regression approach. Drawing on the PROGRESS framework for health equity [57], in WP3B we will investigate in detail the impact of the B-CAP on health inequalities, considering a wide range of characteristics (for example, household-level SES and ethnicity), focusing on respiratory health outcomes for 13,500 children in our BiB data set.

#### Power calculations

In order to explore power of the ITS analysis to detect changes in health outcomes we have consulted a range of epidemiological studies and systematic reviews, along with identification of relevant intervention studies for effect sizes. Our own research has found that a 10μg/m3 increase in NO_2_ is associated with a 9% increase in the odds of low birthweight, while a 5μg/m3 increase in PM2.5 is associated with an 18% increase in odds of low birth weight [58]. For other health outcomes, systematic reviews have shown a 10μg/m3 increase in NO_2_ to be associated with increases in respiratory disease hospital admissions ranging between 0.57-3.5%, and a 0.66% increase in admissions for cardiovascular admissions, with stronger effects among children and the elderly [59–63].

Recent intervention studies (reviewed earlier) offer no consistent results. Based on the evidence reviewed and working on the assumption the B-CAP will reduce NO_2_ by between 12-18μg/m3 we have estimated a 5% reduction in health outcomes (emergency / GP attendances and incidence related to both respiratory and cardiovascular outcomes); and a 2% reduction in adverse birth outcomes. A 5% reduction in emergency attendances in relation to respiratory and / or cardiovascular illness would likely have substantial cost-savings for the NHS [64].

We have reviewed methods to inform power calculations; there are no accepted guidelines for calculating power in ITS designs [65, 66]. Power is dependent on a variety of factors including the length of the time series (with some suggesting 100 observation points required for correct model identification), [67] the balance of time points before and after the intervention, the expected effect size, the extent of autocorrelation between the data points, and sample size per time point. Power increases in a balanced ITS design; in WP3 our proposed study would increase the power by ensuring roughly equal number of data points for the 3 years pre- and 3 years post-implementation. We illustrate the potential power of our analyses for our primary outcome, respiratory health (measured as emergency/GP admissions): in pilot analysis of a subsample of our connected data set (*N* = 316,585, assessed between Jan 2016-Dec 2018) we observed an average of 380 respiratory attendances per week suggesting adequate counts per observation period. Using weekly counts will give us a total of 312 observation points over a 6 year period. Guidance from simulations of Winquist et al. [66] suggests we will have > 90% power to detect a 2% reduction in admissions. For our secondary outcomes (cardiovascular/birth) we will assess counts either weekly or monthly depending on prevalence. Using monthly events a balanced design would give us 72 evenly distributed observations points. We will explore increasing the baseline intervention trend period by 28 months (e.g. 5 years pre-implementation) to ensure we can maintain 100 observation points (which is acceptable if there are no other major changes in pre-intervention trends in that time period) [65].

In WP3B we will focus only on respiratory attendances within the BiB cohort using similar methods. For these analyses we will have fewer events per observation period and so will perform analyses using either weekly or monthly counts.

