#### Analysis methods

For WP3A, demographic information from cBradford (age, sex, ethnicity, IMD and geographic location (ward level of those inside and outside the CAZ)) will be summarised using frequency (%) or mean (SD). For WP3B, information (age, sex, ethnicity, IMD, measures of SES) from the BiB cohort will similarly be summarised. An interrupted time series (ITS) design using segmented regression analysis will be used to estimate levels and trends during specific points in time (segments), where the values of the time-series may change from the previous pattern because changes in air pollution trends as a result of the B-CAP intervention. In segmented regression, terms are included in the model to indicate, for example, the baseline level of the outcome, the implementation of the intervention, and time after the intervention. These effectively fit separate regressions for “segments” so that it is possible to estimate changes in level and trend. The assumption underlying our analyses is that we would expect a slope change in our outcome measure as we expect the implementation of the B-CAP and its effects are gradual.

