We will examine time-series line plots of the health outcomes to aid identification of underlying trends and seasonal patterns of the data. As the outcomes are counts, the Poisson link function will be used in the regression model. Models will be adjusted for age, sex, ethnicity, and measures of SES such as IMD. The coefficients from this regression can be used to estimate the intervention effect (the absolute difference between the predicted outcome based on the B-CAP and its counterfactual value, i.e. the expected values for level and trend if the intervention had not occurred. We will account for the disruption caused as a result of the COVID-19 pandemic, and the subsequent changes in behaviour including alterations to travel behaviour and A&E and GP attendances, through the selection of change points used in the segmented regressions. In England, the first lockdown was implemented on the 23rd of March 2020 and the third ended on the 31st July 2021. We will therefore consider four segments for our analysis: (1) the period prior to the first national lockdown from when clinical data of sufficient quality was available (October 2017 – March 2020); (2) the period spanning the lockdowns (March 2020 – August 2021); (3) the period encompassing the preparation phase for the CAZ (August 2021 - CAZ switch on, this includes other activities within the B-CAP including provision of grants for vehicle upgrades); (4) the period post ‘switch on’ of the charging CAZ). We will conduct an interim analysis at 12 months post-implementation and re-examine analyses 3 years post-implementation.

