### Follow-up

We have included a range of outcome measures that are likely to reflect shorter (A&E/GP attendances related to respiratory and cardiovascular disease), and longer term effects (birth outcomes). The B-CAP is mandated to improve air quality to compliant levels in ‘*as quick a time as possible’*. Based on modelling, the likely impact of measures included within the CAZ, compliance is due to be achieved 1 year post implementation, with gradual ongoing improvements over time. However, research has shown there is no ‘safe’ level of pollution for health, thus any improvements in air quality are likely to have an impact on health, regardless of whether they are above, or below legal limits [58]. Evidence has shown an immediate temporal relationship between increases in pollution and hospital attendances [60] thus we would expect to see an immediate reduction in emergency and GP attendances related to respiratory (adults and children) and cardiovascular (adults only) events provided the B-CAP is successfully implemented. Our other outcomes (birth outcomes) are likely to show an effect in the longer term. We have chosen 3 years as our primary follow-up period to measure effectiveness (with an interim reporting period at 1 year) period in order to provide timely evidence for decision makers, including other local authorities on the health impacts of CAZ approaches to improving air quality. As our primary analysis relies on routine data we have the unique opportunity to revisit our study populations beyond the lifetime of the planned research to provide even longer term follow-ups of the health outcomes outlined in Table 3. We have chosen a 1 year follow up for our process and evaluation outcomes to ensure timely capture of challenges related to implementation, and identification of the proximal effects by which the intervention might have an impact on outcomes.

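### The > 90% power for a 2% reduction rests on a balanced two-period series and was not updated for the four-segment model that will be fitted

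*Protocol article*

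**What the plan says.** In the protocol article, Work package 3, Power calculations, the primary outcome is a weekly count. The pilot subsample (N = "316,585, assessed between Jan 2016-Dec 2018") is the source of the rate: "we observed an average of 380 respiratory attendances per week". The section assumes three years on each side of go-live, hence 312 weekly points, and says that guidance from a published simulation study "suggests we will have > 90% power to detect a 2% reduction in admissions". It attaches no alpha, effect shape, dispersion or autocorrelation value to that figure. The effect expected from the plan is put at 5%.

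The Analysis methods section of the same work package describes a Poisson segmented regression with level and trend terms and adjustment for season. Because of COVID-19 it says "We will therefore consider four segments for our analysis": pre-lockdown, lockdowns (to August 2021), preparation (August 2021 to switch-on) and post switch-on. The start of the first is given as "from when clinical data of sufficient quality was available (October 2017".

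On the shape of the effect, Analysis methods says "we would expect a slope change in our outcome measure as we expect the implementation of the B-CAP and its effects are gradual", while the Follow-up section says "we would expect to see an immediate reduction in emergency and GP attendances".

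For monthly secondary outcomes, Power calculations adds: "We will explore increasing the baseline intervention trend period by 28 months (e.g. 5 years pre-implementation"), in order to keep 100 points.

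**The concern.** The power figure describes a clean series of three years before and three years after. The analysis section no longer uses such a series. In a model with its own level and slope in each segment, the switch-on effect is judged against the segment just before it, and that segment is short. Separating a level or slope change from trend and season costs much more precision than comparing two means.

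At stake is how the primary result is read. If the sentence stands, a null finding could be taken as a well-powered exclusion of a 2% benefit, although the planned model would usually miss an effect of that size.

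**Working it through.** **Inputs from the protocol.** 380 attendances a week; 156 + 156 weeks; rate ratio 0.98 (and 0.95 for the expected 5%); lockdown 23 March 2020 to 31 July 2021 = 495 days = 70.7 weeks; October 2017 to 23 March 2020 = about 129 weeks; go-live in 2022.

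**Assumptions.** Two-sided 5%; two annual harmonics; variance equal to the mean; a scaled count of 380 × 530,000 / 316,585 = 636 a week as an alternative. The preparation segment is 21–73 weeks across the whole of 2022. The Citizen science monitoring section puts its pre-implementation periods in Autumn 2021 and Spring 2022 and its post-implementation periods in Summer and Autumn 2022. That implies go-live around spring–summer 2022, or about 35–50 weeks.

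**Formula.** Power = Φ(|b|/SE − 1.96) + Φ(−|b|/SE − 1.96), where b is the effect on the log scale and SE comes from the inverse Poisson information matrix.

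**The plan's own figure.** Plain contrast: SE = √(2/(156 × 380)) = 0.0058; |ln 0.98| = 0.0202; ratio 3.48; power 93.6% (93.3% if the second total is reduced by 2%). The stated > 90% therefore reproduces. At 380 a week it drops below 90% once dispersion exceeds about 1.14, and it is 69% at dispersion 2.

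**Four segments, separate levels and slopes, 380 a week.**
- Level change of 2%: SE 0.0259 (21-week preparation segment) to 0.0148 (73 weeks). Ratios 0.78 to 1.36; power 12% to 28%.
- Slope change averaging 2% over three years, so reaching 2 × 0.0202 = 0.0404 at year 3: SE 0.30 to 0.047. Ratios 0.13 to 0.86; power 5% to 14%.
- Level change of 5%, |ln 0.95| = 0.0513: ratios 1.98 to about 3.46; power 51% to 93%.
- Slope change averaging 5%, reaching 0.1026: ratios about 0.34 to 2.18; power 6% to 59%.
- Level change detectable with 80% power: 2.80 × SE = 0.0725 to 0.0414, or 7.0% to 4.1%.

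At 636 a week each SE is multiplied by √(380/636) = 0.773.

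| Model and effect | 380/week | 636/week |
|---|---|---|
| Plain before/after, 2% | 93–94% | 99% |
| Four segments, 2% level change | 12–28% | 17–42% |
| Same, spring–summer 2022 go-live | about 17–20% | about 25–31% |
| Four segments, slope averaging 2% | 5–14% | 5–20% |
| Four level shifts, one common trend, 2% level change | 30–46% | 46–67% |
| Four segments, 5% level change | 51–93% | 73–99% |
| Same, spring–summer 2022 go-live | 70–82% | 90–96% |
| Four segments, slope averaging 5% | 6–59% | 7–81% |

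Overdispersion or positive autocorrelation would lower every entry.

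**Monthly points.** 72 + 28 = 100, but 36 + 28 = 64 months before go-live is 5.3 years, not 5. Five years before and three after gives 60 + 36 = 96. Data from October 2017 with go-live in January to December 2022 give 51–63 months before, so 87–99 points in all, including about 16 lockdown months.

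**The case against.** The strongest case for the sentence has several parts.

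- **It is offered as an illustration.** The section says there are no accepted guidelines for power in this design and names autocorrelation and balance as factors. The data are whole-population routine records, so no recruitment depends on the figure. This bears on how serious the fault is. It does not rescue a specific number for the primary outcome that the planned model does not have.
- **The figure comes from a simulation study not seen here.** This stands. A reader might infer that the authors used the plain contrast, or that > 90% can hold only there. The documents do not support either. If lockdown weeks are dropped and a single pre-intervention trend is fitted, a ramp averaging 2% has about 90–93% power at 636 a week (71–76% at 380), for go-live in late September 2022. That is not the four-segment analysis described.
- **The expected effect is 5%, not 2%.** A reader might infer that the study cannot detect 5% either. That is too strong: an immediate 5% step has 70–82% power at 380 a week for a spring–summer go-live. Power for 5% is poor mainly for the slope change.
- **The baseline is not simply lost.** Seventy-one of the last 156 pre-weeks sounds like a 45% loss, but the series starts in October 2017 and keeps 129 + 21 to 73 = 150–202 non-lockdown pre-weeks. The difficulty is the segmentation, not the number of weeks.
- **Gradual and immediate effects can be partly reconciled.** Pollution may fall gradually while attendances respond to it quickly, and the plan will test the gradual assumption. A flat contradiction is not shown, but the effect being powered is still not identified.
- **The 28-month extension is exploratory and conditional.** It concerns monthly secondary outcomes and has no bearing on the headline figure, so it is a minor correction only.

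**Conclusion.** The concern holds as a mismatch between the basis of the power statement and the analysis model. It is not an arithmetic error, since the stated figure reproduces for a simple balanced contrast. For a 2% effect the four-segment seasonal model has about 12–28% power for a level change and 5–14% for a slope change at 380 a week (17–42% and 5–20% at 636). Even the more favourable common-trend form reaches at most about 67%. No four-segment form examined comes near 90%.

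These results rest on the assumed alpha, harmonics, scaled count and go-live date, and on pure Poisson variance, which is the favourable case. A reader might infer that the design is unsound or the primary analysis futile. The documents do not support that: the whole-population data are fixed and an immediate 5% step is tolerably powered. The sentence should be corrected because it would mislead the reading of a null result. The fault does not invalidate the study.

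**What to change.** Replace the > 90%/2% sentence with power, or a minimum detectable effect, from simulation of the four-segment model. Take seasonality, dispersion and autocorrelation from the October 2017 to March 2020 series, and use the full cBradford weekly count. State the result for one named estimand (level change, slope change, or average three-year difference from the counterfactual), and make the effect shape in Analysis methods and Follow-up consistent with it.

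For the monthly outcomes, remove or correct the 100-point statement: 28 extra months is 5.3 years, five years before and three after gives 96 points, and data from October 2017 give fewer than 100, lockdown months included.

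The cost is a short simulation, some rewording and a less favourable stated power. No new data are needed.

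### The 28-month baseline extension is not 5 years, and with usable data from October 2017 no go-live in 2022 gives 100 monthly points

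*Protocol article*

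**What the plan says.** The introduction to Work package 3 sets the comparison window: "We will compare trends of health outcomes collected for 3 years pre, and 3 years post implementation (minimum 6 years data"). The Power calculations section turns this into monthly points: "Using monthly events a balanced design would give us 72 evenly distributed observations points". The same section cites a benchmark for the length of the series, "with some suggesting 100 observation points required for correct model identification". To meet it, the team will explore lengthening the baseline "by 28 months (e.g. 5 years pre-implementation) to ensure we can maintain 100 observation points", a step it calls "acceptable if there are no other major changes in pre-intervention trends in that time period".

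The Analysis methods section of Work package 3 then fixes where the series can begin. The first of its four segments runs "from when clinical data of sufficient quality was available (October 2017 – March 2020").

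Go-live is planned for 2022, with no month given (The Bradford Clean Air Plan; Table 2). The Citizen science monitoring section places one pre-implementation wave in spring 2022 and the first post-implementation wave in summer 2022. Table 3 fixes birth outcomes as monthly and leaves cardiovascular outcomes weekly or monthly. The Power calculations section leaves the cohort analysis (WP3B) weekly or monthly as well.

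**The concern.** One sentence gives two lengths for the same baseline, and only one of them produces the 100 points it promises. Separately, the start of usable data given in the analysis section appears too late for either the promise or, on the implied go-live dates, the 5-year version of it.

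The stake is modest. The power statement in the article (over 90% for a 2% reduction) is made for weekly respiratory counts. For outcomes analysed monthly, the count of 100 is the only numerical indication of adequacy that the article offers. If it cannot be reached from data the plan regards as good enough, a reader will believe the monthly series is longer than it will be. The analysts would otherwise have to draw on records from before the stated quality date without having said so.

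**Working it through.** **Inputs.** 36 months before and 36 after go-live (Work package 3 introduction; Power calculations). Extension of 28 months, also described as 5 years; target of 100 points (Power calculations). Usable data from October 2017 (Analysis methods). Go-live in 2022 (Table 2). Spring 2022 pre-implementation and summer 2022 post-implementation waves (Citizen science monitoring).

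**Step 1: the plan's own figures.**
- Balanced design: 36 + 36 = 72. This matches the article.
- With 28 extra months: 72 + 28 = 100. This matches the article.

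**Step 2: the 5-year description.**
- Baseline after the extension: 36 + 28 = 64 months; 64 / 12 = 5.33 years, or 5 years 4 months.
- A 5-year baseline is 60 months, an extension of 60 − 36 = 24 months, not 28.
- Points with a 5-year baseline: 60 + 36 = 96, which is 4 short of 100.

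**Step 3: what October 2017 allows.** For a go-live on the first day of month m in 2022, whole baseline months = (2022 − 2017) × 12 + (m − 10). Total points = baseline + 36.

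| Go-live | Baseline months | Total points | Short of 100 by |
|---|---|---|---|
| 1 January 2022 | 51 | 87 | 13 |
| 1 May 2022 | 55 | 91 | 9 |
| 1 June 2022 | 56 | 92 | 8 |
| 1 July 2022 | 57 | 93 | 7 |
| 1 August 2022 | 58 | 94 | 6 |
| 1 October 2022 | 60 | 96 | 4 |
| 1 December 2022 | 62 | 98 | 2 |
| End of December 2022 | 63 | 99 | 1 |

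A 64-month baseline from October 2017 would need go-live in February 2023. Even a 5-year baseline is available only from October 2022, later than the monitoring schedule implies.

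**Step 4: how far back 64 months reaches.** Sixty-four months before 1 May 2022 is January 2017; before 1 August 2022 it is April 2017. The extension would therefore use 9 to 6 months of data from before October 2017.

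**Step 5: the competing start date.** The pilot in the Power calculations section used a subsample of the connected data from January 2016. From then to 1 May or 1 August 2022 is 76 or 79 months, so 64 would be available if those records were accepted. The article does not say that they are.

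**The case against.** The strongest reply is that little depends on the 100. The team says only that it will explore the extension, the 5 years is offered as an example, and the benchmark is attributed to some authors after a statement that no accepted guidelines exist. No test or conclusion is tied to it, and no loss of power from having 91 to 94 points in place of 100 has been shown. All of that stands, and it keeps this a matter of correcting a stated figure. It does not remove the contradiction: the stated purpose of the extension is to secure 100 points, and the article's own data start rules that out.

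The second reply is that the pilot shows records back to January 2016, and that October 2017 appears in a description of segments without discussing birth records separately. This also has force. It means the shortfall depends on taking "from when clinical data of sufficient quality was available" at face value. But the pilot counted respiratory attendances in a subsample and shows that records exist, not that their quality is sufficient.

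Two stronger readings are tempting. A reader might infer that the lockdowns breach the condition attached to the extension, since they lie inside the longer baseline. The documents do not establish this. For the latest possible go-live in 2022, the original 36 months begin at the end of December 2019, so the added 28 months always end before the first lockdown on 23 March 2020. The lockdowns fall in the 3-year baseline with or without the extension, and the analysis section already gives them their own segment. A reader might also infer that cardiovascular outcomes must be modelled weekly. The plan makes that choice depend on prevalence and gives no cardiovascular counts, so nothing here settles it.

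**Conclusion.** The point holds as a correction of stated figures. The 28 months and the 5 years disagree by 4 months, or 4 points (100 against 96), and this needs no assumption. Taking October 2017 as the start of usable data and 36 months of follow-up, every go-live date in 2022 leaves the monthly series short of 100. The total is 87 to 99 across the year, and about 91 to 94 if go-live falls between May and August 2022. The May to August window is an inference from the school monitoring waves, because the article gives no month, but the conclusion does not depend on it. It would change only if records from before October 2017 were accepted as adequate.

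The point reaches birth outcomes, and cardiovascular and WP3B analyses if these are monthly. It does not touch the weekly primary outcome, whose 312 points do not rely on the extension.

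**What to change.** In the Power calculations section, make the extension and its description agree: either 28 months, 5 years 4 months and 100 points, or 24 months, 5 years and 96 points. Then choose one of two courses.

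- Keep October 2017 as the start of the baseline. State the attainable monthly count (about 91 to 94 for a May to August 2022 go-live, 87 to 99 for any date in 2022) and say that the 100-point benchmark is not met for outcomes analysed monthly.
- Use records from before October 2017, such as those behind the January 2016 pilot. Say so, justify their quality for the outcomes concerned, and bring the Power calculations and Analysis methods sections into line on the start date.

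The first course costs a few words and a slightly less favourable figure. The second also needs a short statement on data quality. Neither changes the design or the primary analysis.
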